### Sample size

Reviews of behavioural intervention studies have reported small to medium effects of web-delivered interventions aimed at increasing physical activity [84, 85]. Studies that excluded participants who are already active, which most closely represent the current protocol, reported a small-to-medium effect (*d* = 0.28) [84]. Therefore, to detect a similar effect on physical activity between intervention and control group, a total of 134 participants will be required to achieve 80% power with alpha set at *p* < .05. Based on an estimated drop out of 30% from web-based tailored interventions to increase physical activity [84], the final target sample size of 192 participants (48 per group) will be recruited at baseline. The study is powered to detect differences between the intervention group and control group (i.e., parallel 2-arm trial); not between the four study arms.

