### Study design

The *PATHS* study is a pragmatic four-group intervention trial adopting a randomised control design with assessments of primary and secondary outcomes at baseline and 3-month follow-up time points (see Fig. 1). We chose randomisation of individuals within hospitals (rather than randomisation of hospitals or wards) because individual randomisation was more efficient and more feasible with continuous recruitment of the participants; program was delivered to individuals rather than groups so contamination across intervention groups was not considered a major risk [46]. The project comprises three intervention conditions and a no intervention condition, in which participants receive information about the study only. This will serve as a control condition. Each condition includes a group of theory-based BCTs designed to test the additive effects of the specific BCT groups on study outcomes:
**Control condition** – provision of information about physical activity only
**Motivation condition** – provision of information + motivational BCTs
**Self-regulation condition** – provision of information + motivational BCTs + self-regulatory BCTs
**Habit condition** – provision of information + motivational BCTs + self-regulatory BCTs + habit formation BCTs

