After the second meeting, participants will be emailed a personalised login/password, and link to the website so they are able to login to the web-based *PATHS* study platform used to deliver the tailored intervention messages. Participants will be automatically randomly allocated online in an equal ratio to one of the four possible study conditions; a block randomisation will be used with block size of 16. If allocated to one of the three intervention conditions, they will be able to complete the first intervention session on the website immediately after completing the baseline assessments. If allocated to the control condition, they will receive an email directing them to the *Library* site for physical activity relevant information. The *Library* is a sub-section of the website with non-tailored evidence-based information about physical activity,

Across all conditions, participants will be encouraged to use and interact with the web-based *PATHS* platform for three consecutive months, completing sessions every fortnight. At the end of month three, participants will meet with the researcher and will be provided with a GENEActiv activity monitor to be worn for one week immediately post-intervention to assess physical activity. Participants will meet with the researcher again one week after they received the activity monitor to complete the post-intervention questionnaires and return the activity monitor (Time 2). All researchers collecting the data will be blinded to the allocation of participants’ study condition.

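### A total of 134 participants does not give 80% power for d = 0.28: unadjusted power is about 29% at the 3:1 split the design implies, and 134 is the number needed in the control arm alone.

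*Protocol article*

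**What the plan says.** All the inputs to the calculation are in the Sample size section of the protocol article. It draws d = 0.28 from a review of web-delivered interventions in people not already active, and it concludes that "a total of 134 participants will be required to achieve 80% power", "with alpha set at *p* < .05". It then allows for 30% dropout and sets the recruitment target at 192, or 48 per group. It defines the contrast that the power claim covers: "The study is powered to detect differences between the intervention group and control group (i.e., parallel 2-arm trial); not between the four study arms".

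Two other sections fix the allocation. Study design says that "The project comprises three intervention conditions and a no intervention condition", the latter serving as control. Procedure says that participants are "randomly allocated online in an equal ratio to one of the four possible study conditions". The comparison of intervention with control is therefore 144 against 48 at recruitment, a 3:1 split.

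Study analysis plans a mixed model of condition by time (baseline and 3 months). Dropouts have their baseline value carried forward, and both intention-to-treat and completers results are to be reported. The sample-size text mentions no correlation between baseline and follow-up and no one-sided test.

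**The concern.** For a standardised difference of 0.28, a two-group total of 134 is far below what the usual calculation gives. The section states its effect size, alpha, power, contrast and total, so the claim can be tested on its own inputs.

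This is the only power statement in the article and it concerns the primary outcome. The section disclaims power for comparisons among the four arms, so the pooled contrast is the one comparison it claims to have powered. If that claim is wrong, readers will believe that the trial had an 80% chance of detecting the effect it cites as the closest available evidence, when the chance may be well under half. A non-significant result could then be taken as evidence against an effect of that size.

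**Working it through.** **Inputs.** d = 0.28 with SD = 1, alpha 0.05, power 80%, total 134, dropout 30%, target 192 (all from Sample size). Allocation is 1:1:1:1 (Procedure) with three intervention arms and one control (Study design), so the pooled ratio is k = 3. Sidedness is not stated; two-sided is assumed and one-sided is also shown.

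**1. The dropout step reproduces.** 134 / (1 − 0.30) = 191.4, rounded up to 192, or 48 per arm.

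**2. The 134 does not reproduce as a total.** The control-arm size is

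n_control = (1 + 1/k) × (1.960 + 0.842)² / d²

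At k = 3 this is (4/3) × 7.849 / 0.0784 = 133.5. The noncentral t gives 133.97. Both round up to 134 controls, with 3 × 134 = 402 intervention participants and a total of **536**.

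At k = 1 it is 2 × 7.849 / 0.0784 = 200.2, or 201 per group. The noncentral t gives 201.2, or 202 per group, total **404**.

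One-sided totals are 424 (3:1) and 316 (1:1). None of these totals is 134; the number appears only as the control arm of the 3:1 two-sided calculation.

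**3. Power with 134 in total.** Power = Φ(d/SE − 1.960), with SE = √(1/n₀ + 1/n₁).

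| Analysed | SE | d/SE | Power (normal) | Power (noncentral t) |
|---|---|---|---|---|
| 33.5 vs 100.5 | 0.1995 | 1.404 | 28.9% | 28.6% |
| 67 vs 67 | 0.1728 | 1.621 | 36.7% | 36.3% |
| 48 vs 144 (all 192) | 0.1667 | 1.680 | 39.0% | 38.7% |

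One-sided testing with 134 gives about 40% at 3:1 and 49% at 1:1. The last row is a best case. Baseline carried forward sets the change of dropouts to zero, so with 30% dropout in every arm the average difference would shrink to 0.7 × 0.28 = 0.196.

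**4. Using the baseline measurement.** The correlation r is an assumption, because the article gives none. Baseline adjustment multiplies the SD by √(1 − r²); a change score multiplies it by √(2(1 − r)). At 33.5 vs 100.5 and d = 0.28 (normal approximation):

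| r | Baseline-adjusted | Change score |
|---|---|---|
| 0.5 | 37% | 29% |
| 0.7 | 50% | 44% |
| 0.8 | 65% | 60% |

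For 80%, the SD multiplier must be 1.404 / 2.802 = 0.501. That means r of about 0.87 (adjusted) or 0.88 (change score) by the noncentral t.

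**5. Effect that 134 can detect at 3:1 with 80% power.** 2.802 × 0.1995 = 0.559; the noncentral t gives 0.563, so d = 0.56 unadjusted. With adjustment the noncentral t gives 0.49 at r = 0.5 and 0.40 at r = 0.7.

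**The case against.** The arithmetic is not in dispute. The objections concern how firmly it may be read.

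- **The origin of 134 is an inference.** The article shows no formula, ratio or software. Another route exists: a condition-by-time repeated-measures F test with f = 0.14, two equal groups and a correlation of about 0.34 to 0.35 also gives about 134. This stands as a caution about the cause, but it does not rescue the figure. An interaction f of 0.14 in a 2 × 2 design means a difference in change of 4 × 0.14 = 0.56 SD, twice the stated effect. It also needs equal groups, which the allocation does not give, and a correlation that is not stated.
- **The 29% is an unadjusted figure for 134 completers.** The planned model uses baseline, so actual power depends on r. This stands, and 29% should always carry the word unadjusted. With all 192 analysed and no dilution, r = 0.8 would give about 80%, but the planned carrying forward of baseline values works against that.
- **The 3:1 pooling is inferred.** The section speaks of one intervention group and a two-arm trial, and Study analysis names no pooled contrast. Pooling is the natural reading of a claim that excludes comparisons among the four arms. If the split were 1:1, the shortfall would be threefold (404/134) rather than fourfold (536/134).
- **An article may leave the assumed correlation to the full protocol.** That is fair, and its absence is not a fault in itself. The fault is that the inputs printed do not lead to the number printed.
- **No text says how a null result would be read.** That is true; the risk of misreading follows from the claim and is not a stated intention.

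**Conclusion.** The concern holds. On the section's own inputs a total of 134 does not give 80% power. Unadjusted power at d = 0.28, two-sided 0.05, is about 29% at the 3:1 split that the randomisation implies and about 36% at 1:1. The evaluable total needed is 536 at 3:1, four times the stated number, which after 30% dropout would be 536/0.7 = 765.7, or 766 recruited. The exact match between 134 and the 3:1 control-arm requirement makes it likely that one group's size was reported as the total, but the finding does not depend on that explanation.

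The figures assume a two-sided test, three intervention arms pooled against control, 134 analysed, and the same dropout in every arm. Baseline adjustment raises power to about 37% at r = 0.5 and 50% at r = 0.7. It would take r of about 0.87 to make the statement true. The statement must be corrected.

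**What to change.** Keep the 192 recruits and rewrite the Sample size paragraph along these lines:

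> 192 participants will be randomised equally to four conditions. With 30% dropout, about 134 will be evaluable (about 34 control and 100 in the three intervention conditions combined). For pooled intervention against control (3:1, two-sided alpha 0.05) this gives 80% power for d = 0.56 unadjusted, or for d = 0.49 to 0.40 if the correlation between baseline and follow-up is 0.5 to 0.7. Power at d = 0.28 is about 29% unadjusted.

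State the pooled contrast and give the assumed correlation with its basis. If the 134 came from another calculation, print that calculation with all its inputs. Commit to reporting the estimated difference with its confidence interval, and to not reading non-significance as absence of an effect.

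The cost is one reworded paragraph and a less favourable stated figure. The number recruited and the design stay as they are.

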### Study hypotheses

We hypothesise significant increases in physical activity between baseline and 3-month follow-up in the three intervention conditions but no change in physical activity levels in the control groupWe hypothesise that increases in physical activity at 3-month follow-up will be greatest in the habit intervention condition with smaller changes for the self-regulation and motivation conditions.We hypothesise that participants allocated to the habit condition will have maintained the physical activity changes over time relative to the self-regulation, motivation, and control conditions at 3-month follow-upWe hypothesise that higher engagement in the program (e.g., frequency of logins, number of sessions completed, reported relevance and usefulness of the sessions content) will lead to greater change in physical activity at 3-month follow-up in all intervention groups.We hypothesise that the effects of the habit condition on physical activity behaviour will be mediated by the self-reported habit development, effects of the self-regulation condition will be mediated by self-efficacy and planning, and the motivation condition will be mediated by the social cognitive variables of attitudes, motivation, and intention.

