Following the three-month period, participants will be thanked for their study contribution via personal email and text message, and their names will be automatically entered into a prize draw allowing them to win shopping vouchers for their participation (four shopping vouchers, 20 AUD value per each hospital). Participants allocated to the control condition will then be given the opportunity to receive the content from one of the intervention conditions so that they are not prevented from participating in a potentially effective intervention. They will receive login details, password and link to the web-based tailored platform providing them with the option to engage in one of the three intervention conditions, chosen randomly. All study participants will be told that there are four different versions of the same program that differ in content and behaviour change techniques used. Participants will be asked not to share or compare intervention content to avoid study contamination among participants working on the same ward. They will be asked in the post intervention evaluation if they adhered to the aforementioned recommendation.

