**Fig. 2 Fig2:**
[figure not shown]
*PATHS* study – intervention screenshots – content examples

All participants will also have access to *Frequently Asked Questions* page, a sub-section of the website about practicalities of its use (e.g., how to change their password, basic features, tips on navigating through the website). This sub-section of the website has been designed based on piloting previous similar website [66]. Participants will be able to contact an intervention facilitator if they have any additional questions about participating in the study. There will also be an *About* page available – a sub-section of the website that will (1) explain the reasons why the intervention was developed and (2) introduce the *PATHS* study research team to add credibility. A *Frequently Asked Questions* page and an *About* page, also developed from previous investigations piloting the platform, will be slightly different for each intervention condition to account for the differences between conditions.

Participants allocated to the three intervention groups will have access to additional intervention features. Each fortnight, they will be prompted via email to access the website and to answer short online surveys and receive tailored feedback based on the information provided in their responses. Depending on their group allocation (Tables 1 and 2), participants will receive feedback aimed at promoting motivation (motivation group), motivation and self-regulation (self-regulation group), or motivation, self-regulation and prompts for actions (habit group). Information pertinent to the participant’s condition will be delivered via personally-tailored messages presented as text on a webpage accompanied by appropriate pictures and graphs with tailored information (e.g., graphs showing participant’s change in physical activity or weight throughout the intervention). The intervention will include six consecutive sessions that will be presented fortnightly for three consecutive months.

**Table 1 Tab1:** Intervention content for *PATHS* study **-** overview

Session number	Motivation condition	Motivation + self-regulation condition	Motivation + self-regulation + habit condition
1	Motivation and self-efficacy	Motivation, self-efficacy and self-monitoring	Motivation, self-efficacy, self-monitoring and habit development
2	Goal setting	Goal setting and action planning	Goal setting, action planning and forming positive habits

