#### Physical activity

The primary outcome will be measured physical activity over a one-week period prior to the intervention (Time 1) and for a further week immediately post-intervention at the three-month follow-up occasion (Time 2) using accelerometers (GENEActiv Ltd.) [47, 67]. Participants will be asked to wear the unit continuously for the seven day period on the non-dominant upper arm to comply with hospital hygiene regulations. The GENEActiv device is water proof and participants will be informed that they are free to choose whether to wear it while swimming, showering, or sleeping. Data will be collected at 60 Hz epoch frequency. Step counts will be derived from the acceleration data using open-source macros and they will be used as proxy for physical activity [47]. Participants will be supplied with a band specifically designed to fasten the monitor to the upper arm.

Secondary outcomes will be assessed at baseline (Time 1) and post-intervention (Time 2), and will include subjective measures of physical activity, sitting time, sleep, depression, anxiety, stress, quality of life, theory-derived correlates of physical activity and self-reported weight. Demographics, perceived neighbourhood environment, personal need for structure, internet self-efficacy, and planning skills/ability will be assessed at baseline (Time 1) only. Secondary outcomes assessed only at the post-intervention stage (Time 2) will include measures of intervention accessibility, usefulness and satisfaction with the intervention, as well as acceptability of the advice provided. Participants’ website usage (e.g., time spent on pages with specific intervention content, number of website visits) will be assessed throughout the study using Google Analytics.

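### Hypothesis 3 predicts that the habit arm maintains its activity gains, but the only post-baseline measure is the week straight after the programme, so maintenance cannot be tested

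*Protocol article*

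**What the plan says.** Study hypotheses lists five hypotheses. The third states that "participants allocated to the habit condition will have maintained the physical activity changes over time relative to the self-regulation, motivation, and control conditions" and places this at the 3-month follow-up. The second, for the same occasion, expects the largest increase in the habit arm and smaller ones in the self-regulation and motivation arms.

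The timing is fixed in several places:

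- **Length of the programme.** Intervention delivery: "The intervention will include six consecutive sessions that will be presented fortnightly for three consecutive months". Procedure asks participants to use the platform "for three consecutive months, completing sessions every fortnight".
- **Timing of the outcome.** In Procedure, the monitor is handed out at the end of month three, "to be worn for one week immediately post-intervention to assess physical activity". Measures, under Physical activity, says the same: "for a further week immediately post-intervention at the three-month follow-up occasion (Time 2) using accelerometers".
- **Number of assessments.** Study design plans "assessments of primary and secondary outcomes at baseline and 3-month follow-up time points". The abstract and Table 3 agree.
- **Model.** Study analysis specifies a four-condition by two-time mixed model, with baseline and 3-month follow-up as the time levels.
- **After Time 2.** Procedure: "Participants allocated to the control condition will then be given the opportunity to receive the content from one of the intervention conditions". No later assessment is described.

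**The concern.** To show that a change is maintained after a programme, one needs the level reached when the programme ends and the level at some later time. The plan measures the first and not the second.

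What is at stake is interpretation. When the monitor goes on at Time 2, participants have only just come off fortnightly sessions, weekly texts and login reminders. Activity that depends on this prompting cannot be told apart from activity that would continue without it. Yet the article's theory section presents habit formation as the passage of behaviour to automatic control. A favourable habit-arm difference at Time 2, reported under hypothesis 3, could be read as evidence of lasting change when it shows only an effect at the end of the programme. Essentially the same comparison could also be counted as support for two hypotheses.

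**Working it through.** No published figure has to be reproduced here. The check is a count of measurement occasions, followed by a comparison of the contrasts in the two hypotheses.

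**1. Time between the end of the programme and the outcome**

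- Sessions: 6 × 2 weeks = 12 weeks, which the article treats as three months.
- Platform use runs for the full three months. The monitor is issued at the end of month three and worn for one week.
- Gap from the end of the programme to the start of wear: 0 weeks. By the end of wear: 1 week.

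**2. Measurements available for each participant**

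| Quantity | Needed to test maintenance | Planned |
|---|---|---|
| Outcome occasions, including baseline | at least 3 | 2 |
| Post-baseline occasions | at least 2 | 1 |
| Pairs (end of programme, later) | at least 1 | 0 |
| Change scores from baseline | at least 2 | 1 |

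With two time levels, the condition-by-time term estimates only differences between arms in (Time 2 − baseline). It has no component for change after Time 2.

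**3. Contrasts named in hypotheses 2 and 3**

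| Contrast on (Time 2 − baseline) | Hypothesis 2 | Hypothesis 3 |
|---|---|---|
| Habit vs self-regulation | yes | yes |
| Habit vs motivation | yes | yes |
| Habit vs control | not named | yes |

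Read as an end-of-programme difference, hypothesis 3 has 3 contrasts, of which 2 are already in hypothesis 2. Outcome, occasions and model term are the same for all three.

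**4. Could other data supply the missing test?**

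- The questionnaire measures of activity are listed in Table 3 at Time 1 and Time 2 only, so they have the same limit.
- Each of the six sessions asks about activity in the previous week, and the platform stores the answers. These are self-reports taken during the programme, in the three intervention arms only, and the stated model does not use them. They cannot show what happens after the programme ends, and they give no comparison with control.

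**The case against.** Four points deserve weight.

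*The phrase may be loose.* The word maintained could mean that early gains are still present at month three. The stored session self-reports do bear on that reading in the intervention arms, so a reader who infers that the trial collects nothing about the course of activity over time would go too far. But these reports are not the accelerometer outcome, are absent in controls, whom the hypothesis names, and lie outside the stated analysis. They do not make hypothesis 3 testable as written.

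*The two hypotheses are not identical.* A reader might infer that they reduce to one estimate. They do not: hypothesis 3 adds habit versus control, and each hypothesis contains several pairwise contrasts. The supportable statement is that they largely overlap.

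*A later randomised comparison is not ruled out.* A reader might infer from the offer made after Time 2 that none would remain. The offer goes to controls only, so the three intervention arms would stay comparable as randomised. Only a later control comparison would be compromised, to the extent that controls take up the offer. In any case, no later assessment is planned.

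*Maintenance is not central to the article.* The Discussion gives main and additive effects as the primary aim and restates the habit hypothesis only as greatest effectiveness. Neither the abstract nor Implications promises a maintenance result. This stands, and it limits the importance of the point.

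Two other defences fail. The label 3-month follow-up cannot mean three months after the programme, because Procedure and Measures both place Time 2 immediately after it. Nor is this a detail that an article leaves to a fuller document: the hypothesis, the timing and the model are all stated, and they do not fit together.

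**Conclusion.** The point holds. As worded, hypothesis 3 cannot be tested with the planned accelerometer data and the two-level time model: there is one post-baseline occasion, at a gap of 0 weeks from the end of the programme, and there are no pairs of measurements that could show persistence or decay. Under the weaker reading it is testable, but then 2 of its 3 contrasts repeat hypothesis 2.

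This rests on taking maintenance to mean persistence after the programme ends, and on the article describing every planned assessment. It concerns one of five hypotheses and what may be concluded from it. It does not touch the validity of the Time 2 comparison itself, and the documents do not support a claim that the primary analysis is undermined.

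**What to change.** Do one of the following in Study hypotheses:

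1. Delete hypothesis 3; or
2. Merge it with hypothesis 2, worded as the habit arm compared with each of the self-regulation, motivation and control arms on change in physical activity from baseline to the end of the intervention.

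In either case, add a sentence that the trial does not assess maintenance after the intervention ends, and keep to that limit when reporting Time 2 results.

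The cost is one claim given up. No visit is added, and the primary outcome, the mixed model and the sample size stay as they are.
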